## Abstract

**Background:**

Late onset sepsis is a leading cause of death and morbidity in preterm infants. Despite optimal antibiotic treatment, sepsis related mortality and morbidity is still high. Pentoxifylline (PTX) is a methylxanthine with promising immunomodulatory properties, which can be used as an additional therapy next to antibiotics in preterm infants. PTX is increasingly used off-label in neonatal intensive care units, however up till now no dose finding study has been done for PTX in this specific population. The aim of this study (PTX-trial) is to determine the optimal dose of PTX in preterm infants (gestational age < 30 weeks) with (suspected) late onset sepsis. Dose finding in this particular population is unique, since for most drugs used in neonates the optimal dosage has not been investigated in phase II dose-seeking studies.

**Methods:**

The PTX-trial is a prospective open label sequential dose-optimization study with an adapted continual reassessment method. An up-and-down dose-response design will be used, with dose step-up and step-down titration after every 3 patients. The PTX starting dosage will be 30 mg/kg/day in 6 hours as described in most previous neonatal studies. Efficacy is defined by means of biochemical and clinical parameters. Toxicity in these vulnerable patients is unwarranted. The optimal dose is defined as the ED75 (i.e., clinically and chemically effective dose for 75% of patients) in preterm neonates with late onset sepsis. We plan to include 30 neonates to determine the optimal dose using this study design. Subsequently, the optimal dose will be validated in 10 additional preterm neonates. In parallel, pharmacokinetics of PTX and its metabolites will be described as well as longitudinal evaluation of metabolomics and proteomics.

**Discussion:**

The study has been approved by the Regional Medical Ethics Board of Erasmus Medical Center University Rotterdam (MEC 2019-0477) and registered at Clinicaltrials.gov (NCT04152980). Results of the main trial and each of the secondary endpoints will be submitted for publications in peer-reviewed journals.

**Trial registration:**

Clinicaltrials.gov, NCT04152980, Registered November 6th, 2019

## Background

Neonatal sepsis is the leading cause of death and morbidity in preterm neonates worldwide [1–3]. The incidence of late onset neonatal sepsis, defined as sepsis onset after 72 hours after birth, is up to 20% among very low birth weight infants (VLBW, birth weight < 1500 gram) in developed countries [3, 4]. Sepsis therapy in preterm neonates consists of antibiotic treatment, support of vital functions and comfort [5]. Despite adequate antibiotic treatment many preterm neonates do not recover from sepsis, with overall mortality rates of late onset sepsis around 18%, and up to 36% in preterm neonates infected with gram negative organisms [3]. An excessive neonatal inflammatory response with sepsis is associated with increased mortality, but also major morbidity characteristics such as bronchopulmonary dysplasia (BPD), necrotizing enterocolitis (NEC), retinopathy of prematurity (ROP) and cerebral palsy (CP) [3]. In humans, maturation of the adaptive immune system occurs after birth, thus making the innate immune system largely responsible for protection against micro-organisms in the first weeks. Preterm birth results in an additional reduced ability to respond to pathogens characterized by reduced expression of surface innate immune receptors and immature intracellular downstream responses. A consequently reduced anti-inflammatory response and dysregulation of the immune system plays a major role in organ injury in these preterm infants [6, 7].

Pentoxifylline (PTX), a methylxanthine, is currently registered only for peripheral artery disease treatment in adults and is used off label in newborn infants with sepsis. PTX is a promising therapeutic compound, which can be repurposed as adjuvant therapy next to antibiotics for preterm infants with sepsis [8]. PTX acts as a cAMP-phosphodiesterase inhibitor that suppresses TNF-α and modulates important parts of the inflammatory response. Also, the production of other inflammatory cytokines is reduced, such as IL-1α, IL-6, and IL-8, by phagocytes [9] and their subsequent effects are prevented, such as leukocyte adherence, migration, and degranulation [10]. Furthermore, PTX has beneficial effects on endothelial cell function and coagulation in sepsis and exerts its cellular effects on erythrocytes, platelets, endothelial cells, polymorphonuclear leukocytes, macrophages, and fibroblasts [11]. Next to its action on the inflammatory response, PTX also has been suggested to improve the microcirculation [12], one of the key features of sepsis. Given these mechanisms of PTX, it is a high potential candidate for adjuvant immunomodulatory therapy in neonatal sepsis.

PTX has already been shown to have beneficial effects in humans, especially in preterm infants [13–16] in a dose of 30 mg/kg in 6 hours. In a recent meta-analysis of six trials that included in total 416 neonates, it was shown that PTX therapy in this dosage regimen was associated with a decrease in all-cause mortality during hospital stay in infants with late onset sepsis (risk ratio of 0.42) [15]. Furthermore, no side effects have been reported due to PTX treatment in neonates. Overall, there have been multiple suggestions, including clinical studies, that PTX is well tolerated and might improve the recovery and increase the survival of preterm infants suffering from sepsis [14, 15]. Nevertheless, pharmacokinetic (PK) and pharmacodynamic (PD) data of PTX and its active metabolites (M1, M4, M5) are largely lacking. Consequently, target concentrations in this particular population are yet absent, as well as the effect of certain physiological parameters and maturation on clearance. The maturational effect has shown to have an extensive impact for multiple compounds in neonates [17, 18], but has only been poorly described for PTX in neonates [19].

In our Neonatal Intensive Care Unit (NICU) at the Erasmus MC, Rotterdam, the Netherlands PTX is increasingly used in preterm infants with severe sepsis according to a local clinical sepsis protocol based on recent literature. In some countries, such as Poland and Austria, PTX is already used as standard of care therapy for preterm infants with suspected sepsis. Up until now, most clinical studies with PTX to treat sepsis in neonates used the same dosage of 30 mg/kg/day (5 mg/kg PTX per hour for 6 hours every 24 hours) during 3 consecutive days. Research to define optimal dosages based on precise effects, side-effects and the adequate concentration-effect profile of PTX and its active metabolites in preterm neonates is still missing. In the absence of dose finding data, treatment of these patients with the current dose is potentially suboptimal (either under- or overexposure). Finding the optimal dose of PTX is of utmost importance to potentially increase the effectiveness and safety in preterm infants, which can only be obtained from dose seeking research in this vulnerable population. Thus, a dose optimisation study is the next most mandatory step in the drug research and development process for PTX in neonatal sepsis. Because optimal PTX dosing as well as target concentrations of PTX and its metabolites are lacking, we combined these in a prospective dose finding study. The primary objective is to define the ED75 (i.e., clinically and chemically effective dose for 75% of patients) in preterm neonates with late onset sepsis. Simultaneously, as a secondary objective the PK and PD of PTX and its active metabolites will be investigated.

## Methods/Design

### Study settings

Patient recruitment will be performed in two level IV NICUs (Erasmus University Medical Center – Sophia Children’s Hospital, Rotterdam, the Netherlands and Poznan University of Medical Sciences, Poznań, Poland. Recruitment started in December 2019 and is expected to continue for 24 months.

### Participants

Patients are eligible for inclusion if the following criteria are met (1) gestational age below 30 weeks; (2) suspected of sepsis, defined as blood drawn for inflammatory biomarkers and blood culture; (3) increased inflammatory biomarkers at moment of suspicion (C-Reactive Protein (CRP) > 50 mg/L and/or Interleukin-6 (IL-6) > 500 pg/mL); (4) patients with a post-natal age older than 72 hours (late onset sepsis) (see Fig. 1). It is reasonable to assume that patients with (severe) sepsis are most likely to benefit from PTX treatment, and that pharmacokinetics and dynamics are different compared to patients without or with mild sepsis. We aim to investigate the optimal dose in those patients who are likely to benefit the most. Therefore, we have incorporated chemical biomarkers IL-6 and CRP in our inclusion criteria, because these biomarkers are associated with subsequent sepsis severity and can be determined at the moment of sepsis suspicion [20]. By incorporating these biomarkers in our inclusion criteria, they could help select patients with possible culture proven sepsis early in the disease process.

**Fig. 1 Fig1:**
[figure not shown]
PTX-trial study flowchart. NEC, necrotizing enterocolitis; AUC, area under the curve; AB, antibiotics

Exclusion criteria concern (1) patients in whom PTX therapy cannot be started within 24 hours of start of antibiotic treatment for any reason; (2) patients with major congenital defects (e.g. congenital heart disease, pulmonary, or gastrointestinal anomalies); (3) patients that already participated in the trial during an earlier episode of late onset sepsis; (4) patients with a pH below 7 in two consecutive blood samples, with at least 1 hour between the blood samples, at start of sepsis episode; and (5) IL-6 values exceeding 25000 pg/mL at time of onset. High IL-6 values represent severe episodes of sepsis and high IL-6 values are associated with high mortality rates [21].

We expect to include 30 neonates to determine the optimal dose using this study design. Planned sample sizes in dose finding studies are generally dictated by practical constraints rather than statistical constraints related to type I error rate or minimum power for testing a specific hypothesis [22, 23]. Generally, cohort sizes in dose finding studies differ between 1-5 patients. A cohort size of 1 is limited by the fact that results could be different by chance, however a cohort consisting of 5 patients will take a long period of time to complete due to the low incidence of severe LONS. In this study we chose for 3 patients in each cohort. Earlier dose finding trials in neonates have shown that a sequential dosing of 10 doses will be sufficient to define an optimal dose, resulting in a total number of 30 neonates to be included. Subsequently, the optimal dose will be validated in 10 preterm neonates.

### Pharmacological intervention

The drug PTX (Trental®, 100 mg/5 ml, Sanofi-Aventis, Austria) will be administered intravenously in a fixed concentration of 5 mg/ml diluted with NaCl 0,9%. The starting dose will be 5 mg/kg/h for 6h every 24 hours for 3-6 days (30 mg/kg/day), which is the most commonly reported dosing regimen in studies until now and has been safely tolerated in these studies, without any reported severe adverse events [16, 24–30]. The duration of therapy will be at least 3 days and can be extended to a maximum of 6 days if judged necessary by the treating physician. In order to find the optimal dose our explicit aim is to study different PTX dosages, next to antibiotics. To do so, dosages will be adjusted with upward and downward dose adjustments (see Fig. 2), based upon clinical and chemical response and adverse drug reactions with decision on the up/downward dose adjustments after each cohort of 3 patients who will receive the same dosage. Intra-individual dose adjustments will not be performed, but the up/down dose adjustments are predefined (Fig. 2).

**Fig. 2 Fig2:**
[figure not shown]
PTX-trial experimental dose-steps of tested dosages

PTX therapy will be started as soon as possible and ideally concomitant with antibiotic therapy, but no later than 24 hours after start of antibiotic treatment. Based on previous experience PTX seems most effective if initiated in the early stages of sepsis [31]. If administration is delayed until overt septic shock occurs, it may have deleterious effects, such as systemic hypotension [31]. We hypothesise that PTX has a therapeutic window, where no adverse side effects in preterm infants with the previously used dosages have yet been reported.

The maximal dose per hour that will be tested is 5 mg/kg/h continuously, in order to avoid high peak concentrations. It has been predetermined that higher dosages are out of the scope of this trial. This study design does not aim nor allows to explore the highest tolerated dose.

### Primary objective

The principal aim is to determine the ED75, which is defined as a both clinical and chemical effective dose for 75% of patients. The clinical outcome is considered effective when the clinical response to PTX is adequate. Therefore, we have defined a set of clinical endpoints we consider to be inadequate. The biochemical outcome is considered effective if the CRP response is adequate.

In order to asses effectiveness we will determine if the PTX dose is adequate in every individual patient in every cohort of 3 patients who receive the same dosage.

#### An adequate response – criteria for effectivity

An adequate PTX dose is determined by 3 co-primary outcome variables: biochemical response, clinical response and adverse drug reactions. (1) An adequate biochemical response is determined by means of repeated CRP measurement in blood during PTX treatment. We hypothesize that CRP levels will decrease in patients with PTX treatment as was shown in previous studies [16]. CRP levels will be measured in blood at time of onset and 24, 48 and 72 hours after onset. An area under the curve (AUC) will be calculated for each patient. A CRP AUC below the median CRP AUC of the previous cohort considered to be adequate. (2) The clinical response is considered to be inadequate if the following clinical endpoints are reached: mortality, necrotizing enterocolitis Bell stage 3, pH below 7 in 2 consecutive blood samples with at least 1 hour between the 2 samples after start of sepsis treatment and/or the need to start NO therapy with indication pulmonary hypertension after start of sepsis treatment. (3) The dose is considered inadequate if severe adverse drug reactions take place. All adverse events observed spontaneously by the parents or caretakers or observed by the investigator or his staff will be recorded. Potential severe adverse drug reactions will be evaluated by the research group. To assess the causality an algorithm by Du et al [32] will be used. To assess severity the International Neonatal Consortium (INC) Neonatal Adverse Event Scale will be used [33].

After inclusion of each 3 consecutive patients (that receive the same dosage), the efficacy of that specific PTX dose will be analyzed based on clinical effect, biochemical effect and adverse drug reactions. The subsequent dose for the next cohort of 3 patients will be based on the outcome (success/failure) of the previous cohort of patients and decreased/increased in accordance with the predefined dosages (up-and-down method in small samples) [34]. The following dosage for subsequent subjects in this study will be determined by the predefined decision rules (see Fig. 3). The decision rule allows to decrease the dosage when therapy is successful and increase the dosage when therapy fails.

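### The pH and NO failure endpoints are timed from the start of sepsis treatment and NEC stage 3 has no start time, so an event before the first PTX infusion can be scored as a failure of the assigned dose

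*Protocol article*

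**What the plan says.** All places are in the protocol article.

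- **An adequate response – criteria for effectivity.** Four events make the clinical response inadequate. Low pH is one of them, defined as "pH below 7 in 2 consecutive blood samples with at least 1 hour between the 2 samples after start of sepsis treatment". A second concerns pulmonary hypertension, namely "the need to start NO therapy with indication pulmonary hypertension after start of sepsis treatment". Both of these run from the start of sepsis treatment. The other two are death and Bell stage 3 NEC, and the latter carries no start time.
- **Background.** Sepsis therapy is described as antibiotics, support of vital functions and comfort. PTX is an addition to it.
- **Pharmacological intervention.** PTX is to start as early as possible, "no later than 24 hours after start of antibiotic treatment".
- **Participants, exclusion criteria.** Excluded are "patients in whom PTX therapy cannot be started within 24 hours of start of antibiotic treatment for any reason", and infants with "pH below 7 in two consecutive blood samples, with at least 1 hour between the blood samples, at start of sepsis episode". The gastrointestinal exclusion concerns congenital anomalies. No listed criterion mentions NEC or NO therapy.
- **Primary objective.** The clinical outcome is effective when the clinical response to PTX is adequate.
- **Decision rule (text after Fig. 3).** Failure argues for a higher dose and success for a lower one. Without an adverse drug reaction, two increase votes in a cohort of three raise the dose, and one leads to a decrease.
- **Ethics and dissemination.** The investigator and attending physicians may withdraw an infant before PTX is given, at their discretion.

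**The concern.** The clock for two of the failure endpoints can start up to 24 hours before the infant receives any study drug. The stated aim is the response to PTX, so the time anchor and the aim do not agree.

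Take an infant who starts antibiotics at hour 0, has the two low pH values or starts NO between hours 4 and 12, and receives the first infusion at hour 18. The low-pH exclusion does not apply, because the event was not at the start of the episode. The endpoint text then classes the infant as a clinical failure. An infant who presents with NEC stage 3 and otherwise meets the entry criteria is classed in the same way.

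Such a failure says nothing about the dose. It still counts as an increase vote for the next cohort and enters the ED75 as a failure at that dose. Because the endpoint steers dosing during the trial, a correction at the final analysis alone would come after later infants had been allocated their dose.

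**Working it through.** **The plan's own figure.** 3 infants per cohort × 10 sequential doses = 30, as stated. The article gives no alpha, power or effect size, so there is no power calculation to repeat, and the fix leaves 30 unchanged.

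**Inputs.** From the article: cohort size 3; at least 2 increase votes needed to raise the dose when no adverse drug reaction occurs; up to 24 hours between antibiotics and PTX. Assumed, because the article gives neither: *p*, the probability that an infant fails for reasons other than a pre-PTX event, and *q*, the probability of a pre-PTX event. The two are taken as independent, and each failure as one increase vote.

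**Step 1: a cohort that contains one pre-PTX failure.**

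Without such an infant, P(increase) = 3*p*²(1 − *p*) + *p*³. With one, the dose rises only if at least one of the other two also fails: P(increase) = 1 − (1 − *p*)².

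| *p* (assumed) | Without | With one |
|---|---|---|
| 0.10 | 0.028 | 0.190 |
| 0.25 | 0.156 | 0.438 |
| 0.40 | 0.352 | 0.640 |
| 0.50 | 0.500 | 0.750 |

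For *p* = 0.25: 3 × 0.0625 × 0.75 + 0.0156 = 0.156, and 1 − 0.75² = 0.438. The higher values of *p* matter here. Biochemical success means a CRP AUC below the previous cohort's median, so with no dose effect about half of the infants would fail on CRP alone.

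**Step 2: averaged over all cohorts.**

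The per-infant failure probability becomes *p* + *q*(1 − *p*). Observed success at a dose with true success of 75% becomes 0.75(1 − *q*). The chance of at least one affected infant in 30 is 1 − (1 − *q*)³⁰, and the expected number is 30*q*.

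| *q* (assumed) | P(increase), *p* = 0.25 (base 0.156) | P(increase), *p* = 0.50 (base 0.500) | Observed success at true 75% | At least one in 30 | Expected in 30 |
|---|---|---|---|---|---|
| 2% | 0.174 | 0.515 | 73.5% | 45% | 0.6 |
| 5% | 0.200 | 0.538 | 71.3% | 79% | 1.5 |
| 10% | 0.248 | 0.575 | 67.5% | 96% | 3.0 |

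**Step 3: effect on the ED75.** To show 75% success, a dose would need true success of 0.75/(1 − *q*): 76.5%, 78.9% and 83.3% for the three rates. If success rises with dose, the estimated ED75 moves upward. This applies even in cohorts where the affected infant is outvoted.

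**The case against.** The strongest defence is that safeguards already exist. The low-pH exclusion uses the same criterion as the pH endpoint at the start of the episode. The exclusion of IL-6 above 25000 pg/mL removes some very severe presentations. PTX is ideally given together with antibiotics, so the window may often be short. Physicians may withdraw an infant before PTX. At least three of five researchers judge each case, with control by the DSMB, and the objective speaks of response to PTX, so they might disregard an earlier event. Figures 1 and 3 are not shown, and a fuller protocol may say more.

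Part of this stands. A reader might infer that eligibility removes no infant who has already met a failure endpoint. The low-pH exclusion contradicts that for pH at onset. A reader might also infer that one such infant drives the dose up. The decision rule contradicts that too: one increase vote against two decrease votes lowers the dose. And averaged over cohorts, low event rates give modest shifts.

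What does not stand is that the safeguards close the gap. None is a timing rule. Withdrawal is discretionary and not tied to the endpoints, and the evaluators are told nowhere to set aside events before the infusion. Nor is this detail left to another document: the article states an anchor for pH and NO, and that anchor can precede the drug.

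**Conclusion.** The concern holds in a limited form. The stated time anchor for pH and NO, and the absence of one for NEC stage 3, allow an event before exposure to be scored as a failure of the assigned dose. This conflicts with the stated aim of measuring response to PTX. The error has one direction: it raises the chance of a dose increase and lowers the observed success that feeds the ED75.

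Its size cannot be fixed from the article, which gives no pre-PTX event rate. The effect within an affected cohort is large. The average effect runs from small at an assumed 2% to a loss of 7.5 percentage points in observed success at 10%. These figures assume independence, one vote per failure and no adverse drug reactions. The upward shift of the ED75 also requires that success rises with dose. How one infant's clinical and CRP results combine into a vote is not clear from the text shown.

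A reader might conclude that new exclusions for NEC or NO therapy are needed. The article does not support that step: they would change the study population, and the scoring problem can be solved without them. This is a cheap correction worth making, of moderate weight.

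**What to change.** Reconcile the exclusion criteria, the PTX start window, the primary objective and the effectivity criteria as follows.

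1. Count the pH, NO and NEC stage 3 endpoints only when they are first reached after the start of the first PTX infusion.
2. State that an infant who met one of them before that time does not count as a clinical failure in the cohort decision or in the pooled and clinical ED75, and is replaced in the cohort for these purposes. The rules on adverse drug reactions are unaffected.
3. Check that event times can be placed before or after the first infusion. The article does not say whether they are recorded in that form.

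The cost is amendment wording and the replacement of a few infants: 0.6 to 3 expected in 30 at assumed rates of 2% to 10%. No change to eligibility, tested doses or clinical management is needed, and 30 evaluable infants remains the target.
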